#### 8.4.19. Fundoscopy

Stereoscopic biomicroscopy of the full fundus is performed using a 90 Dpt lens (Volk) or equivalent to check for signs of inflammation and retinal detachment.

#### 8.4.20. Dark adaptation (DA)

After 3 minutes of bleaching with bright white light (pupil dilation), a staircase procedure is used to estimate detection thresholds for red and green. The whole measurement lasts for approx. 40 minutes.

#### 8.4.21. Ganzfeld electroretinogram (ERG)

The Ganzfeld electroretinogram (ERG) is the record of diffuse electrical response to light stimuli, generated by neural and non-neural cells in the retina. Depending on recording conditions (i.e. scotopic or photopic), stimulus intensity, wavelength, frequency or stimulus duration, the function of various retinal cells can be isolated. Further details of the test procedures are described in the Procedure Manual.

#### 8.4.22. Spectral domain optical coherence tomography (SD-OCT)

Patients will be examined in mydriasis using a Spectralis HRT+OCT system (Heidelberg Engineering, Heidelberg, Germany). Briefly, perpendicular line and volume scans are recorded to quantify micro-anatomical changes in the macula before (baseline) and after (follow up) treatment. The patient is asked to look at a visual cue while eye-tracking software will correct for involuntary eye movement. Baseline recordings will be identified to allow precise follow-up recordings based on the same anatomical landmarks used for eye-tracking. The untreated eye will be recorded first, followed by the treated one.

#### 8.4.23. Fundus autofluorescence (FAF)

The Spectralis HRT+OCT system described above will be used in the same session to record FAF, a measure of retinal pigment epithelial metabolism and viability (Schmitz-Valckenberg et al., 2008). Central 55° recordings will be made with optional extensions towards the outer limits of the treated area, if they are not covered by the central recordings. The untreated eye will be recorded first, followed by the treated one.

#### 8.4.24. Fundus photography (FP)

Fundus of all patients will be recorded in mydriasis for documentation of posterior segment changes. This includes 9 separate wide-angle recordings (central, superior, superior-nasal, nasal, nasal-inferior, inferior, temporal-inferior, temporal, temporal-superior). The untreated eye will be recorded first, followed by the treated one.

#### 8.4.25. Angiography

ICG Angiography

Indocyanine Green is a dye, which fluoresces in the infra-red light. The infra-red waves have the ability to penetrate the retinal layers making the circulation in deeper layers visible when photographed with an infra-red sensitive camera. The dye is applied by intravenous injection and flows through the body to reach the choroidal and retinal circulation. Due to its nature it stays in the retinal and choroidal vessels, this allows to see and identify the distinct outlines of the vessels of the choroid.

Fluorescein Angiography (FA)

Perfusion characteristics will be assessed in mydriasis using a wide-angle objective after intravenous bolus administration of 10% fluorescein sodium (500mg in 5ml; Novartis Pharma AG, Bern, Switzerland).

The central fundus of the treated eye will be recorded with sequential photographs in the first 45 seconds after injection. At 1 and 5 minutes after injection the same 9-view recordings will be performed in both eyes.

#### 8.4.26. Topical steroids and antibiotics

Moxifloxacin eye drops 0.5% are administered 4 times a day and dexamethasone gel 0.5% is administered 4 times a day for 21 days, starting at day -1.

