| 26.                                            | Systemic steroids b                                    | x (Day -1)    | x   | x  | x  | x       |          |          |          |          |                      |           |           |           |           |
| 27.                                            | Topical steroids and antibiotics c                     | x (Day -1)    | x   | x  | x  | x       | x        | x        |          |          |                      |           |           |           |           |
| 28.                                            | Subretinal injection of rAAV8 vector                              |               | x   |    |    |         |          |          |          |          |                      |           |           |           |           |
| 29.                                            | VFQ25                                                             | x             |     |    |    |         |          | x        |          | x        | x                    | o         | o         | o         | o         |
| 30.                                            | Psychiatric examination                                           | x             |     |    |    |         |          |          |          |          |                      |           |           |           |           |
| 31.                                            | Brief Symptom Inventory (BSI)                                     | x             |     |    |    |         | x        | x        | x        | x        | x                    |           |           |           |           |
| 32.                                            | Psychological counselling d                            |               | x   | x  | x  | x       | x        | x        | x        | x        | x                    |           |           |           |           |
| 33.                                            | study specific scale, A3-PRO                                      |               |     |    |    |         | x        | x        | x        | x        | x                    | x         | x         | x         | x         |
| 34.                                            | Adverse event recording                                           |               | x   | x  | x  | x       | x        | x        | x        | x        | x                    | x         | x         | x         | x         |

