| 35.                                            | Concomitant medication                                            | x             | x   | x  | x  | x       | x        | x        | x        | x        | x                    | x         | x         | x         | x         |
| 36.                                            | HIV Test                                                          | x             |     |    |    |         |          |          |          |          |                      |           |           |           |           |

o: optional, if control deemed necessary by investigator

a including but not limited to: Anti-AAV8 capsid ELISA

b Systemic steroids will be given orally 1.0mg/kg for appr. three weeks starting at day -1 and then tapered off after day 19 as deemed appropriate by the investigator (e.g. 40/30/20/15/10mg).

c Moxifloxacin eye drops 0.5% 4x/d & 0.1% dexamethasone gel 4x/d for 21d starting at day -1

d at patient's need and discretion

e if the previous tests have shown improved results

f if CCT is not feasible

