| cataract formation                           | 1-5%                                               | 9%                     | 10-20%                               |
| transient intraocular hypertension           | 5%                                                 | 0%                     | 5%                                   |
| corneal erosion                              | 5-20 %                                             | 5-20 %                 | 5-20 %                               |

**Table 2:** Risks of complications during 23g PPV referring to literature, previous NHP studies and expected rates for the planned trial. [1] Wilkinson et al., 2013 [2] Lee et al., 2012 [3] Wykoff et al., 2010.

Regarding 2) there is a risk for a loss of vision due to ophthalmic immune reactions to the vector (indirect) or due to direct effects of the vector (however, pre-clinical

[figure not shown]

studies showed no toxic effects with up to 10 fold higher concentrations). If any immune reaction should be triggered by the vector, this might include non-infectious inflammation of the pigment epithelium (epitheliitis), retina (retinitis), vitreous cavity (vitritis) or uveal tissue (uveitis). None of these have been reported in any previous clinical trial involving AAV in ocular gene transfer.

Such effects may result in a significant deterioration of visual function (decrease in VA of  $\geq 15$  letters) and might also occur after initial improvement. A vulnerable period for direct and/or indirect (immunogenic) effects due to the viral packaging protein of the vector would be the first two weeks (time of concomitant steroid treatment). No clinical trial has as of yet reported immune-reaction to the transgene (even in systemic gene transfer). It therefore seems unlikely that a direct or indirect effect due to transgene expression would occur after ocular gene transfer in the immune-privileged subretinal space.

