**Visit 7****D30 ( $\pm$  5 days)**

- Vital signs (O)
- Urine pregnancy test
- Hematology/ basic chemistry (O)
- CRP, IgG, IgM
- Immunopathology
- PCR of rAAV8 genome (O)
- Visual Acuity, BCVA (ETDRS)
- Basic ophthalmological exam (miosis)
- Contrast sensitivity (PR charts)
- Flicker Fusion Frequency
- Colour Constancy (chromatic adaption) (O)
- Anomaloscopy
- Cambridge Colour Test / Farnsworth D15
- IR Video Pupillography

[figure not shown]

- 4306 - MP-1 Microperimetry (20°)
- 4307 - Funduscopy (mydriasis)
- 4308 - Dark adaptation test
- 4309 - ff-ERG (scotopic and photopic)
- 4310 - sdOCT
- 4311 - FAF
- 4312 - FF
- 4313 - Angiography (O)
- 4314 - Topical steroids and antibiotics
- 4315 - VFQ25
- 4316 - Brief Symptom Inventory (BSI)
- 4317 - Psychological counselling
- 4318 - Study specific scale, A3-PRO
- 4319 - Adverse event recording
- 4320 - Concomitant Medication
- 4321
- 4322

## Visit 8

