#### 8.4.27. Systemic steroids

Systemic steroids will be given orally at 1.0mg/kg for approximately 3 weeks starting at day -1 and then tapered off after day 19 at the discretion of the investigator (e.g. 40/30/20/15/10mg).

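### Topical dexamethasone strength is contradictory (0.5% versus 0.1%), and the steroid visit marks do not match the stated durations, so steroid exposure at the Day 30 escalation review is only partly defined

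*Supplement*

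**What the plan says.** All references are to protocol version 5.0, the latest in the supplement.

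- **Topical strength and course.** Section 8.4.26: "dexamethasone gel 0.5% is administered 4 times a day for 21 days, starting at day -1". Flowchart footnote c: "0.1% dexamethasone gel 4x/d for 21d starting at day -1". Section 6.1 gives no steroid regimen that would settle the difference.
- **Topical visit marks.** The flowchart row "Topical steroids and antibiotics c" is marked at day -1, D0, D1, D2, D3, D14 and D30. The Visit 7 (D30) list in section 8.2 includes "Topical steroids and antibiotics" without the sign for an optional item.
- **Systemic course.** Section 8.4.27: "1.0mg/kg for approximately 3 weeks starting at day -1 and then tapered off after day 19 at the discretion of the investigator". Flowchart footnote b agrees in substance. The example taper has five dose steps and no step length.
- **Systemic visit marks.** The flowchart row for systemic steroids is marked from day -1 to D3 only. The Visit 6 (D14) list in section 8.2 includes topical but not systemic steroids.
- **Risk narrative.** Section 7.5, on the vulnerable period for effects of the viral packaging protein, says it "would be the first two weeks (time of concomitant steroid treatment".
- **Use of the data.** Section 7.2.1 makes severe vector-related intraocular inflammation that does not respond to treatment a primary ocular safety item, and section 7.4 makes it a reason to discontinue the trial. Section 3.1 bases each escalation decision on Day 30 data. Section 8.4.35 has changes in medication recorded at every visit.

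**The concern.** A prescriber working from the flowchart and one working from section 8.4.26 would use different strengths, and each would be following the protocol. In a first-in-human trial that is a practical safety matter in itself.

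It also bears on how the safety data are read. Steroids are given as immunosuppression, and a primary ocular safety item is inflammation despite treatment. Section 7.2.3 does not expect effects of the transgene product earlier than two weeks after surgery. The period from about day 14 to Day 30 is therefore the one in which the DMC needs to know what each eye was receiving. In that period the topical marks conflict with the stated course and the systemic course passes into an open taper. With three patients per cohort, a quiet eye on steroids and a quiet eye off steroids are different evidence.

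**Working it through.** **Inputs.** Strengths and topical course: section 8.4.26 and footnote c. Systemic course: section 8.4.27 and footnote b. Marks: flowchart and section 8.2. Visit windows: D14 ± 3 days and D30 ± 5 days, from the flowchart. The plan has no sample size calculation, alpha or power that bears on this point, so the check is a day count and a comparison of passages.

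**1. Strength.** 0.5 / 0.1 = 5. Everything else in the dexamethasone instruction is the same in the two places.

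**2. The plan's own end day.** The protocol has a Day 0, so 21 days starting at day -1 end on -1 + 20 = day 19. This reproduces the day after which section 8.4.27 starts the systemic taper, and it is also the end of the topical course in both topical texts.

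**3. Topical steroids at D30.** The D30 window is day 25 to day 35. The gap from the last topical day is 25 - 19 = 6 days at the shortest, 30 - 19 = 11 nominally, and 35 - 19 = 16 at the longest. The mark at D30 is outside the stated course throughout the window.

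**4. Systemic steroids at D14.** The D14 window is day 11 to day 17. It lies wholly inside the full-dose period to about day 19, yet the flowchart and the Visit 6 list carry no systemic steroid item.

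**5. The two weeks in section 7.5.** Fourteen days end on day 12 if counted from day -1, or day 13 if counted from Day 0. Both are earlier than day 19 plus a taper.

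**6. The taper.** With five steps of L days each after day 19, the last day is 19 + 5L. L is not stated, so the values below are assumptions.

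| Days per step (assumed) | Last taper day | Relative to the D30 window (day 25 to 35) |
|---|---|---|
| 1 | 24 | before it |
| 2 | 29 | inside it |
| 3 | 34 | inside it |
| 5 | 44 | after it |
| 7 | 54 | after it |

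A patient may thus be on or off systemic steroids at the D30 visit and in either case comply with section 8.4.27.

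**The case against.** The strongest reply is that most of the regimen is stated consistently. The two systemic texts agree on dose, start, approximate duration and taper. The two topical texts agree on frequency, start and 21 days. Actual medication is recorded at each visit. All of this stands, and it rules out several stronger readings that a reader might draw:

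- *That the inflammation endpoint has no defined treatment background.* The agreed elements above contradict this. The background is partly defined.
- *That the flowchart ends systemic steroids at D3.* The row refers to footnote b, which gives about three weeks and a taper. The blank at D14 is a missing mark and not a rival end day.
- *That section 7.5 sets a two-week course.* It is risk narrative and prescribes no stop day. The wording is loose and should be aligned.
- *That contradictions cause the on/off systemic variation at D30.* It comes from the discretionary taper, which both systemic texts state in the same way. Reconciling the text would not remove it.
- *That the dose cohorts cannot be compared.* Section 10.4 is descriptive, uses individual line charts and gives no descriptive parameters for the cohorts of three. Nor does escalation rest on one look: eyes are examined from D0 to D3, at D14 and at D30, and serious events reach the DMC within one day.

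It can also be said that a visit mark may mean recording rather than administration. That is possible, but the documents do not say so, and the topical mark at D30 disagrees with its own footnote. None of these replies touches the difference in strength.

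**Conclusion.** The contradiction in strength is established from the text alone: five-fold, in the latest version, with no other passage to settle it. The mismatches between marks and durations are also established. Topical steroids are marked 6 to 16 days after the stated course ends, and systemic steroids are unmarked at a visit inside the full-dose period. The wording of section 7.5 is a lesser inconsistency of the same kind.

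The consequence for the data is narrower than the text errors might suggest. Topical exposure at the Day 30 review is contradictory and systemic exposure is left open, so the treatment background of the inflammation endpoint is only partly defined. The range of day 24 to day 54 for the end of the taper rests on an assumed step length of 1 to 7 days. The D30 conflict rests on reading a visit mark as administration. The difference in strength depends on neither assumption and is enough to require correction.

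**What to change.** 1. The sponsor must reconcile section 8.4.26, section 8.4.27, flowchart footnotes b and c, the two steroid rows of the flowchart, the Visit 6 and Visit 7 lists in section 8.2, and the remark in section 7.5. Which strength or duration is right is for the sponsor to say; this review takes no position. The flowchart should also state whether a mark on a steroid row means administration or a check.
2. In the Day 30 data for the DMC, show each patient's actual topical and systemic steroid status at each inflammation assessment. This leaves the investigator's discretion over the taper untouched and makes its effect visible.

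The cost is a text correction, submitted as an amendment under section 13, and one derived variable from the medication records that section 8.4.35 already requires. No additional visit or examination is needed.

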#### 8.4.27. Systemic steroids

Systemic steroids will be given orally at 1.0mg/kg for approximately 3 weeks starting at day -1 and then tapered off after day 19 at the discretion of the investigator (e.g. 40/30/20/15/10mg).

#### 8.4.28. Subretinal injection of rAAV8.hCNGA3 vector

The study treatment is described in section 6 briefly and in detail in the Procedure Manual.

#### 8.4.29. VFQ25

The NEI-VFQ-25 is a 25-item vision-specific questionnaire that collects information about how the patient's vision affects his/her life in 3 areas (General Health and Vision, Difficulty with Activities, Responses to Vision Problems). The NEI-VFQ-25 assesses the influence of visual impairment on functioning and specific aspects of health-related quality of life. The interviewer-administered version of the NEI-VFQ-25 will be used for all patients and will be interview-administered by the study site.

#### 8.4.30. Psychiatric examination

A basic psychiatric examination is performed at screening to ensure that the patient does not suffer from a psychiatric disorder and is not at risk for recurrence of such a disorder. Patients should not be under high pressure due to achromatopsia and/or have high and unrealistic expectations regarding the treatment outcome.

#### 8.4.31. Brief symptom inventory (BSI)

The brief symptom inventory assesses psychological stress and is administered as a questionnaire in interview version. It will be performed by a psychologist or a psychiatrist.

#### 8.4.32. Psychological counselling

The patient has the possibility of psychological counselling with a specialist who does not belong to the study team.

#### 8.4.33. Study specific scale, A3-PRO

In addition to the widely used VFQ25 (see above), which may not be sensitive for the treatment effects in the study population, a study-specific scale was developed in an interview version to be used at selected study visits. A3-PRO assesses the subjectively perceived effects of the treatment.

#### 8.4.34. Adverse event (AE) recording

Open questions regarding changes in health status since last visit are asked by the study physician at the beginning of each study visit.

[figure not shown]

#### 8.4.35. Concomitant medication

At each visit changes in dosing / medication are recorded by the study staff.

#### 8.4.36. HIV Test

Blood for a HIV test will be withdrawn

### 9. Documentation of Trial Data

All original study data from all screened and enrolled patients will be entered into the electronic study database. Original hardcopy documents will need to be signed and dated. GCP-conform monitoring is performed by the CRO of the study as agreed in the monitor manual with the principal investigator on behalf of the sponsor. Any correction on study documents needs to be initialized and dated. All handwriting must be readable. Incorrect entries must still be readable but struck out.

### 10. Biometrical Planning and Analysis

#### *10.1. Trial Design*

This is an open, mono-center trial with fellow-eye comparison.

Due to the characteristics of a phase I trial a dose-escalation design was chosen and due to the fact that there is no effective, approved therapy and this is a safety trial no control condition is foreseen. As a consequence of this, there will be no blinding / randomization procedure. The development of visual function and morphology will be tested against the fellow-eye.

The small sample size, as well as the particularity and rareness of the disease CNGA3-related achromatopsia, led to a monocentric study concept.

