#### **Treatment:**

Each cohort will receive a different, increasing dosage of viral vector genome particles. Three cohorts of patients are planned with low, medium and high dose administration levels up to  $1 \times 10^{11}$  of rAAV8 incorporating the therapeutic expression cassette.

After standard three-port 23G pars plana vitrectomy, balanced salt solution will be used to induce a localized primary retinal detachment in a controlled fashion. Vector solution will be applied using disposable 41G extendible subretinal injection needles within a standard 23G body to fit the port system. Administration will be unilateral (worse eye) in each patient.

**Primary Endpoint:** Safety as the primary endpoint will be assessed by clinical examination of ocular inflammation (slit lamp, fundus biomicroscopy, angiography, perimetry or electrophysiology). Systemic safety will be assessed by vital signs, routine clinical chemistry testing (including CRP, ESR) and full/differential blood counts. Immunopathology essays will include specific enzyme-linked immunosorbent assays for humoral antibodies against rAAV8 capsid protein. Biodistribution will be monitored by polymerase chain reaction studies on rAAV8 genome in blood, urine, saliva and lachrymal fluid.

**Statistical Methods:** AEs and SAEs will be documented using line listings and tabulations (MetraCad code will be applied). Descriptive analysis will include line charts for individual patients. Standard errors and means will also be displayed using line charts. This will be done for the raw measurements and for the difference between treated and untreated control eye within each patient.

Descriptive parameters will be given for the full cohort (n=9) but not for the sub-cohorts (n=3). Additionally correlation analysis will be performed in a purely descriptive manner for the comparison of subjective and objective measurements. For each subject and measurement, the delta of the value for the interventional eye minus the mean of control eye values over time will be determined. In scatter plots for pairs of variables (measurements pooled over subjects) the association between these deltas will be displayed.

**Time Schedule:** Start of trial November 2015, end of recruitment November 2016, end of trial November 2017, duration of trial per patient: one year with four years of follow-up.

[figure not shown]

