## 8.4. Non-ophthalmological and ophthalmological Procedures

All procedures should be performed in the sequence given by the flowchart, whenever possible. If feasible, the same investigators should perform the examinations for the study duration. Advanced test procedures, such as, but not limited to BCVA, microperimetry and pupillography, will be performed by study personnel after method-specific training.

If not specified differently, all tests described here will be performed according to the Flowchart of Visits and Procedures in *both* eyes.

All ophthalmological procedures will be performed in a fixed sequence, testing the study eye first and the fellow eye afterwards.

[figure not shown]

More details of all examination procedures can be found in the Procedure Manual in its current version as approved by the Principal Investigator.

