#### Ophthalmological procedures

All tests described will be performed in a fixed order. The treated eye will be examined first, followed by the untreated eye.

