### ***10.4. Statistical Analysis***

AEs and SAEs will be documented using line listings and tabulations (MetraCad code will be applied). Descriptive analysis will include line charts for individual patients. Standard errors and means will be displayed also using line charts. This will be done for the raw measurements and for the difference between treated and untreated control eye within each patient.

Descriptive parameters will be given for the full cohort (n=9) but not for the sub-cohorts (n=3).

Additionally correlation analysis will be performed in a purely descriptive manner for the comparison of subjective and objective measurements. For each subject and measurement, the delta of the value for the interventional eye minus the mean of control eye values over time will be determined. In scatter plots for pairs of variables (measurements pooled over subjects) the association between these deltas will be displayed.

[figure not shown]

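### The reason given for having no masking, that there is no control, conflicts with the fellow-eye comparison; acuity and contrast testing and OCT/FAF reading could be partly masked

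*Supplement*

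**What the plan says.** Section 10.1 opens with "This is an open, mono-center trial with fellow-eye comparison". It then reasons that, since no effective approved therapy exists and "this is a safety trial no control condition is foreseen", masking falls away: "As a consequence of this, there will be no blinding / randomization procedure". The sentence that follows is "The development of visual function and morphology will be tested against the fellow-eye".

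Section 10.4 plans individual line charts, means and standard errors, and adds: "This will be done for the raw measurements and for the difference between treated and untreated control eye within each patient". The synopsis, under Treatment, fixes the eye to be treated: "Administration will be unilateral (worse eye) in each patient".

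Section 8.4 sets a general order, study eye before fellow eye. The subsection Ophthalmological procedures repeats it: "The treated eye will be examined first, followed by the untreated eye". Sections 8.4.22 to 8.4.24 (OCT, FAF, fundus photography) set the reverse order, untreated eye first. Section 8.4 also asks that the same investigators examine throughout if feasible. It says that advanced tests such as BCVA, microperimetry and pupillography "will be performed by study personnel after method-specific training". No masked examiner, masked image reader or reading centre appears in the text shown. Further test detail is left to a Procedure Manual that is not among the documents.

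**The concern.** Masking an assessor to which eye was treated does not need a separate control arm. It needs only a comparison between eyes, and this plan has one. The single reason offered for having no masking therefore does not support that decision.

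What is at stake is the difference between the eyes. An examiner who knows the treated eye may press harder for one more letter in it, or a reader may grade its image differently. Such an effect starts after treatment, so subtracting a screening value would not remove it. It is also separate from practice or fatigue caused by a fixed order of testing. BCVA matters twice: it is a secondary efficacy endpoint (section 7.1), and a loss of letters is an ocular safety criterion (section 7.2.1) and a ground for discontinuation (section 7.4). Section 10.5 adds an interim analysis for negotiations with industrial sponsors interested in moving towards phase III, so the between-eye results may be used outside the trial team.

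**Working it through.** The plan states no figure that could be reproduced. Section 10.2 says that no sample size estimation was made, and gives no effect size or standard deviation. The check is therefore a comparison of passages.

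1. **Is there a control?** Section 10.1 says none is foreseen, then names the fellow eye as the comparator. Section 10.4 calls that eye the control and plots the within-patient difference. For function and morphology the answer is yes.

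2. **Does the stated reason lead to no masking?** If the phrase about no control condition means no separate arm, it explains why patients are not randomised between arms. It has no bearing on whether the person testing or grading two eyes of one patient knows which was treated.

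3. **Do the procedures reveal the treated eye?** Yes, under either order. An operator told to start with the treated eye (8.4, Ophthalmological procedures) or with the untreated eye (8.4.22 to 8.4.24) must know which is which. The two orders also differ and need reconciling.

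4. **Which measures can be affected?**
 - BCVA and contrast sensitivity: letter charts, where the examiner's prompting can matter. Exposed.
 - OCT and FAF: exposed wherever the reading involves judgement.
 - Flicker fusion (8.4.13): the patient adjusts the frequency. Cambridge Colour Test (8.4.16): forced choice. Microperimetry (8.4.18): button press with eye-movement correction. Less exposed to the examiner.
 - Pupillography and ERG: recorded responses. Less exposed.
 - VFQ25, BSI and A3-PRO: patient-level, so masking by eye does not apply.

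5. **How large could it be?** Unknown. As an illustration only, assume that encouragement adds 1 to 3 letters to the treated eye and that the between-eye change has an SD of 5 to 6 letters. With n = 9, SE = SD/√9, giving 5/3 = 1.67 and 6/3 = 2.00 letters. The shift is then between 1/2.00 = 0.5 and 3/1.67 = 1.8 standard errors. Against a 15-letter loss it is 1/15 = 7% to 3/15 = 20% of the threshold. Only the nine patients and the 15 letters come from the protocol. The assumed SD is also for a change from screening, whereas section 10.4 describes the difference between eyes without that subtraction.

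**The case against.** The strongest reply is that this is an open, nine-patient, first-in-man trial whose primary aim is safety. Efficacy endpoints are all secondary and exploratory, the analysis is descriptive, and no test is planned that a small shift could tip. The paragraph opens by declaring a fellow-eye comparison, so the remark about no control can fairly be read as no separate arm. The patient and surgeon cannot be masked. The worse eye is treated and the same people examine throughout if feasible, so an examiner who saw the patient at screening may guess the eye. The Procedure Manual might also contain masking steps.

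Much of this stands and lowers the weight of the point. It does not rescue the reasoning: the absence of a separate arm is no ground for leaving a between-eye comparison unmasked, and a masking step in the manual would contradict section 10.1.

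A reader might go further and infer any of the following; the documents do not support them.
- That every functional endpoint is biased by the examiner. Sections 8.4.13, 8.4.16 and 8.4.18 describe tests that are mainly driven by the patient.
- That image graders are documented as knowing the treated eye, or that worksheets label it. No graders and no such worksheets are described. Unmasked grading is inferred from the blanket statement in 10.1 and the lack of any masked-reading step.
- That dose should be masked too. Cohorts are treated one after another at one site (section 3.1), so the date gives the dose away, and section 10.4 plans no descriptive parameters by cohort.
- That imaging is done treated eye first. For OCT, FAF and fundus photography it is the reverse.

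**Conclusion.** The point holds in a limited form. Section 10.1 derives the lack of masking from a premise that its own next sentence and section 10.4 contradict, and the testing orders in 8.4 disclose the treated eye. The likely effect is on BCVA, contrast sensitivity and any judged reading of OCT and FAF images.

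Neither the size nor the direction of the bias can be established from the documents. That it favours the treated eye is plausible but assumed, and the 0.5 to 1.8 standard errors above rest wholly on assumed letters and an assumed SD. They should not be cited as an estimate. Because the analysis is descriptive and exploratory, this is an inexpensive improvement to the between-eye results and the letter-loss measure. It is not a flaw that invalidates the trial.

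**What to change.** 1. **Section 10.1.** Delete the inference from no control condition to no masking. State that the patient and surgeon are unmasked, and that OCT and FAF images are coded for treatment status and visit before the existing readers grade them.

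2. **Sections 8.4, Ophthalmological procedures, and 8.4.22 to 8.4.24.** Replace the treated/untreated order, which also differs between sections, with one right/left order for these tests. Right/left labels on forms would achieve nothing while the order still follows treatment status.

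3. **BCVA and contrast sensitivity from D14 on.** Where feasible, have them run by existing trained study personnel who are not told which eye was treated, and ask the patient not to disclose it.

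Slit-lamp and other safety examinations stay unmasked. So does pupillography, where section 8.4.17 names the study eye as the one stimulated, and fluorescein angiography, where only the treated eye has the early sequence (section 8.4.25). No dose masking is proposed.

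The cost is the coding of image files and revised instructions, with no new procedures, visits or patients. The protocol gives no staffing, so whether unmasked knowledge can be kept from enough personnel has to be checked on site. Masking will be imperfect, because surgical signs, cataract or the knowledge that the worse eye is treated may reveal the eye.
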